### Study visits and follow-up

2.7

The investigator will obtain informed consent from each participant before initiating any protocol-related procedures. Eligible participants will be contacted by telephone and scheduled to attend the trial center within one week (Visit 1). During Visit 1 and 4, the investigator will collect relevant information, including demographic data, medical history, medication use, and conduct a physical examination. Participants will then be randomized into either the experimental or control group. In this trial, participants will take FZYX or placebo three times a day for 12 weeks. All participants will undergo scheduled testing and evaluations, including cardiopulmonary exercise testing (CPET), echocardiography, 12-lead electrocardiogram (ECG), routine blood tests, routine urine tests, and blood biochemical tests, including N-terminal pro-B-type natriuretic peptide (NT-proBNP), serum electrolytes, liver and kidney function assessments, coagulation indices, and hemorheology examination. In Visits 2 and 3, participants will undergo the same tests and evaluations as in Visit 1, except for echocardiography and CPET. Follow-up visits 1–8 will consist of telephone follow-ups to record Minnesota Living with Heart Failure Questionnaire (MLHFQ) scores, FRAIL scale scores, all-cause mortality, and composite endpoint events. The detailed follow-up schedule is shown in Table 2.

**Table 2 T2:** Measurement items and points of data capture.

Items	Lead-in period	Treatment period				Follow-up period	
	-7∼-1D	-1∼0D	4W ± 3D	8W ± 3D	12W ± 3D	16,20,24,28W ± 5D	34,40,46,52W ± 5D
	Screening	Visit 1	Visit 2	Visit 3	Visit 4	Follow-up 1–4	Follow-up 5–8
Patients							
Eligibility screen	✓						
Informed consent	✓						
Relevant information^a^	✓						
Allocation	✓						
Outcomes							
CPET		✓			✓		
Echocardiography		✓			✓		
ECG		✓	✓	✓	✓		
Routine blood test		✓	✓	✓	✓		
Blood biochemical test^b^		✓	✓	✓	✓		
Routine urine test		✓	✓	✓	✓		
NYHA functional class		✓	✓	✓	✓		
6-MWT		✓	✓	✓	✓		
TCM syndrome score		✓	✓	✓	✓		
MLHFQ score		✓	✓	✓	✓	✓	✓
FRAIL scale		✓	✓	✓	✓	✓	✓
Composite endpoint event		Record at any time					
All-cause mortality							
Adverse event							

a Related Information includes: demographic data, medical history, medication use.

b Blood biochemical tests, includes: N-terminal pro-B-type natriuretic peptide (NT-proBNP), serum electrolytes, liver and kidney function assessments, coagulation indices, and hemorheology examination; D, day; W, week.

### Outcome measures

2.8

#### Primary outcome

2.8.1

The primary evaluation measure is peak VO_2_.

#### Secondary outcomes

2.8.2

(1)All-cause mortality;(2)Composite endpoint events (treatment abandoned due to worsening heart failure, successful resuscitation after cardiac arrest, malignant arrhythmia, nonfatal stroke, heart failure hospitalization);(3)6-minute walking distance (6MWD);(4)NYHA functional class;(5)Serum NT-proBNP levels;(6)Echocardiography: LVEF, E/e', and others;(7)TCM syndrome scores;(8)Minnesota Living with Heart Failure Questionnaire (MLHFQ) scores;(9)Blood rheology (fibrinogen, whole blood viscosity, platelet aggregation test, erythrocyte sedimentation rate, and others);(10)FRAIL scale.

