### Sample size estimation

2.2

The primary efficacy index of this trial is peak oxygen uptake (peak VO2), as demonstrated in previous related studies (27–29). It is anticipated that the peak oxygen uptake after treatment will be 16 ml/kg/min in the control group and 17.6 ml/kg/min in the experimental group, with a standard deviation of 3.1 ml/kg/min between the two groups. The sample size was calculated using PASS 15.0. The sample size was estimated by comparing the means of two samples in a completely randomized design, using a two-sided test with a significance level of *α* = 0.05 and power (1-*β*) of 0.80. With a 1:1 allocation between the experimental and control groups, the sample size for each group was estimated to be 60 participants. Considering a potential 20% attrition rate, 75 participants were included in each group, resulting in a total of 150 participants.

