### Statistical collection and analysis

2.10

Study data will be collected at each center using standardized paper-based Case Report Forms (CRFs). Participants will be provided with a private space to complete the quality of life form to address privacy concerns. Two-tailed tests will be applied with *P* < 0.05 as the significance threshold. No adjustments for multiple testing will be performed for secondary endpoints, as they are exploratory. Analyses will be conducted using SPSS 23.0 and R 4.3.1. Primary outcome: Analyzed using ANCOVA adjusted for baseline peak VO₂, age, and sex. Secondary continuous outcomes: Assessed via mixed-effects models for repeated measures. Non-normally distributed data will use bootstrap CIs (10,000 replications). Binary/categorical data: Analyzed using chi-squared or Fisher's exact test. Ordinal outcomes: Evaluated via proportional odds models.

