Previous studies of TCM for HFpEF have encountered three major issues. First, many face methodological flaws. The current RCT designs for TCM in HFpEF lack rigor, with improper execution of randomization, blinding, allocation concealment, and reporting biases, all of which undermine study credibility. Secondly, some trials rely solely on modern diagnoses, neglecting TCM symptom selection, which hinders subject “homogenization” and impacts clinical efficacy. Modern medicine classifies by disease, while TCM uses symptom differentiation. Integrating both is essential for standardizing research subjects. Third, hard endpoints like cardiovascular death and rehospitalization are often overlooked (38). Prognostic indicators require long observation periods and significant resources. In contrast, easier-to-detect, shorter-term indicators are commonly used (39). Yet, given HFpEF's severity, more trials should focus on mortality as the primary endpoint.

This study has three key strengths justifying the trial. First, the protocol follows SPIRIT guidelines, ensuring high-quality clinical evidence. Second, patient diagnoses combine modern HFpEF criteria with TCM's Qi-Yin deficiency and blood stasis syndrome, integrating disease and syndrome. Third, the study evaluates long-term prognostic outcomes in addition to objective HFpEF tests. In conclusion, this multicenter, randomized controlled trial evaluates FZYX for HFpEF treatment, aiming to provide high-quality, evidence-based support for its efficacy and safety. Additionally, this study integrates Chinese and Western medicine, potentially guiding alternative treatment strategies.

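### The secondary composite omits death and counts cardiac arrest and stroke only in survivors, so a patient who dies without an earlier component is scored as a non-event

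*Protocol article*

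**What the plan says.** Section 2.8.2 (Secondary outcomes) gives the composite as item 2: "Composite endpoint events (treatment abandoned due to worsening heart failure, successful resuscitation after cardiac arrest, malignant arrhythmia, nonfatal stroke, heart failure hospitalization". Mortality stands apart as item "1)All-cause mortality".

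Both are followed by telephone after the 12-week treatment period. Section 2.7 says that follow-ups 1–8 record "FRAIL scale scores, all-cause mortality, and composite endpoint events", and Table 2 places the last of these at week 52.

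Section 2.10 gives the analysis: "Binary/categorical data: Analyzed using chi-squared or Fisher's exact test". It also sets the status of these outcomes: "No adjustments for multiple testing will be performed for secondary endpoints, as they are exploratory". Nothing in the article says how a death enters the composite, and nothing brings fatal stroke, fatal arrest or cardiovascular death into it.

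The Discussion says of earlier trials that "hard endpoints like cardiovascular death and rehospitalization are often overlooked". It names as a strength of this one that "the study evaluates long-term prognostic outcomes in addition to objective HFpEF tests".

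**The concern.** Two of the five components are conditional on survival. An unsuccessful resuscitation and a fatal stroke are worse than the events that count, yet neither counts. Sudden death out of hospital does not count either. Under a comparison of proportions, such a patient is indistinguishable from one who completed 52 weeks without incident.

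Moving a patient from a non-fatal to a fatal event therefore lowers that arm's composite rate. If one arm has more deaths, or a larger fatal share among its serious events, its composite result improves for the wrong reason. The result could then be read as evidence on prognosis, which the Discussion presents as a strength of the design.

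**Working it through.** **1. The plan's own figure.** The article gives no event rate or power for the composite. Its only sample-size calculation is for peak VO2 (section 2.2): "16 ml/kg/min in the control group and 17.6 ml/kg/min in the experimental group", SD 3.1, two-sided alpha 0.05, power 0.80.

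- n per group = 2 × (1.96 + 0.842)² × 3.1² / 1.6² = 2 × 7.85 × 9.61 / 2.56 = 58.9, so 59 by the normal approximation. The t-test solution is 59.9, so 60.
- Attrition of 20%: 60 / 0.80 = 75 per group, 150 in total.

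This reproduces and does not depend on how the composite is defined.

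**2. How each course is scored under section 2.8.2.**

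| Course | Counted? |
|---|---|
| Non-fatal stroke | yes |
| Fatal stroke, no earlier component | no |
| Arrest, resuscitated | yes |
| Arrest, not resuscitated, no earlier component | no |
| Heart failure hospitalisation, then death | yes |
| Documented malignant arrhythmia, then death | yes |
| Treatment given up for worsening heart failure, then death | yes |
| Death from any cause, no earlier component | no |

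**3. Size when only mortality differs.** Assumptions, not taken from the article: constant hazards over one year, non-fatal hazard λ = 0.25 in both arms, death hazard μ = 0.05 in arm A and 0.15 in arm B.

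- As written, P(component before death) = λ/(λ+μ) × (1 − exp(−(λ+μ))).
  - A: 0.25/0.30 × (1 − exp(−0.30)) = 0.833 × 0.259 = 21.6%.
  - B: 0.25/0.40 × (1 − exp(−0.40)) = 0.625 × 0.330 = 20.6%.
- With death included, P = 1 − exp(−(λ+μ)): A 25.9%, B 33.0%.
- All-cause mortality alone, P = 1 − exp(−μ): A 4.9%, B 13.9%. Of 75 patients that is about 3.7 and 10.4 deaths.

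The arm with three times the death hazard looks better by 1.0 point, about 0.7 of a patient in 75. The larger effect is what goes missing: a disadvantage of about 7 points (33.0 − 25.9) does not appear.

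**4. Size when the fatal share differs.** Suppose both arms have the same total rate of serious events, and a share f of these is fatal with no earlier component. The risk ratio as written is (1 − f_FZYX)/(1 − f_control).

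- f = 30% on FZYX, 10% on control: 0.70/0.90 = 0.78.
- f = 50% on FZYX, 10% on control: 0.50/0.90 = 0.56.

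The true ratio for total events is 1 in both cases. The shares are assumed.

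**5. In counts, 75 per arm (assumed).**

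| Non-fatal + deaths without earlier component | As written | With death |
|---|---|---|
| Control 11 + 1; FZYX 6 + 6 | 14.7% v 8.0% (Fisher P = 0.30) | 16.0% v 16.0% |
| Control 8 + 0; FZYX 4 + 5 | 10.7% v 5.3% (Fisher P = 0.37) | 10.7% v 12.0% |

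At this trial size, these examples distort the estimate and its direction. They do not produce a spurious significant result.

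**The case against.** The best defence is that the two outcomes are complementary: a non-fatal composite beside all-cause mortality, listed next to each other and both followed to week 52. Excess deaths would show in the mortality outcome. In step 3 that outcome separates the arms by about 9 points, while the composite moves by 1. This stands as a reason for moderate weight. It does not correct the composite's own comparison, which is tested separately. Nor does the article label the composite as non-fatal.

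Several stronger readings are tempting but unsupported:

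- A reader might infer that every death from stroke, arrest or heart failure is scored as event-free. Only a death with no earlier component is. Hospitalisation, malignant arrhythmia and abandoned treatment carry no survival condition.
- A reader might infer that the composite is biased whatever happens. With equal mortality and equal fatal shares there is no distortion between arms.
- A reader might take the composite for the trial's main clinical-event outcome. The article does not call it that, and section 2.10 treats secondary outcomes as exploratory.
- A reader might convert the Introduction's 5-year survival of 35%–40% into 17–19% deaths a year (1 − 0.40^(1/5) to 1 − 0.35^(1/5)). That figure follows a first hospitalisation. This trial enrols stable NYHA II–III patients and excludes life expectancy under one year, so the figure is not a basis for expected deaths here.
- A reader might see a contradiction with the Discussion's remark on overlooked hard endpoints. The trial does collect all-cause mortality, so there is none, although leaving death out of the composite sits awkwardly beside that remark.

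**Conclusion.** The point holds as a should-fix for an exploratory secondary outcome. The definition is stated, not left open: death is absent and two components require survival. The direction of any distortion follows from that definition alone. It arises only if deaths or fatal shares differ between arms.

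Its size cannot be fixed from the article, which gives no event rates. Under the assumed hazards the composite shifts by 1.0 point towards the arm with more deaths and hides a disadvantage of about 7 points. Under the assumed fatal shares, the risk ratio falls to between 0.56 and 0.78 with no true difference in total events. The working also assumes that the composite is analysed as a binary outcome, which is how section 2.10 reads although it does not name the composite. Peak VO2 and the 75 per group are unaffected.

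**What to change.** Before unblinding, amend section 2.8.2 and the registry entry so that the composite:

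- includes all-cause death, or cardiovascular death with other deaths handled as a competing event;
- counts cardiac arrest whether or not the patient was resuscitated, and stroke whether fatal or not;
- keeps the other three components as they are.

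Keep all-cause mortality as its own outcome and report each component separately by arm.

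The cost is small: a short amendment, no new data collection for all-cause death (it is already recorded to week 52), and no change in sample size. All-cause death brings some dilution by non-cardiac deaths. Cardiovascular death avoids that, but cause of death must then be classified. Timing matters, because a change made after unblinding would look driven by the data.

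If the sponsor prefers a non-fatal composite, the minimum is to label it so, treat death as a competing event, and always present it beside all-cause mortality.

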### Safety assessment and adverse events report

2.9

Detailed observation and reporting of all types of drug-related allergic reactions (including rash), gastrointestinal reactions (such as nausea, vomiting, diarrhea), neuropsychiatric disorders (including insomnia, headache, dizziness), and abnormal laboratory test results. Laboratory tests include routine blood tests (white blood cell count, red blood cell count, hemoglobin, platelets), routine urine tests (urine leukocytes, urine protein, occult blood, urine glucose), liver function tests (alanine transaminase, aspartate transaminase, total bilirubin, gamma-glutamyl transferase, alkaline phosphatase), renal function tests (serum creatinine, blood urea nitrogen), serum electrolytes (serum potassium, sodium, chloride), and 12-lead ECG. Any serious adverse events occurring during the trial must be immediately reported to the principal investigator and the ethics committee. Additionally, a “Serious Adverse Event” form must be completed.

### Statistical collection and analysis

2.10

Study data will be collected at each center using standardized paper-based Case Report Forms (CRFs). Participants will be provided with a private space to complete the quality of life form to address privacy concerns. Two-tailed tests will be applied with *P* < 0.05 as the significance threshold. No adjustments for multiple testing will be performed for secondary endpoints, as they are exploratory. Analyses will be conducted using SPSS 23.0 and R 4.3.1. Primary outcome: Analyzed using ANCOVA adjusted for baseline peak VO₂, age, and sex. Secondary continuous outcomes: Assessed via mixed-effects models for repeated measures. Non-normally distributed data will use bootstrap CIs (10,000 replications). Binary/categorical data: Analyzed using chi-squared or Fisher's exact test. Ordinal outcomes: Evaluated via proportional odds models.

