**Methods:**

This multicenter, double-blind, randomized controlled trial will be conducted across seven tertiary hospitals in China. We will enroll 150 participants aged 18–80 years with confirmed HFpEF (Qi-Yin deficiency and blood stasis syndrome) meeting inclusion criteria. Participants will be randomly assigned (1:1) to the FZYX group or the placebo group, ​with both groups receiving standardized Western medical therapy according to the National Heart Failure Guideline 2023. The 12-week intervention phase will be followed by 40-week safety follow-up. The primary outcome will be maximal peak oxygen uptake (peak VO_2_). Secondary outcomes will include composite endpoint events, all-cause mortality, 6-minute walking distance (6MWD), New York Heart Association (NYHA) functional class, serum N-terminal pro-B-type natriuretic peptide (NT-proBNP), echocardiographic variables, Minnesota Living with Heart Failure Questionnaire (MLHFQ) score, TCM syndrome scores, and the FRAIL scale.

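### Section 2.10 lists no time-to-event method, so by elimination mortality and the composite, followed to week 52, fall under a chi-squared or Fisher test that ignores event timing and incomplete follow-up

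*Protocol article*

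**What the plan says.** - **Outcomes.** The Secondary outcomes section (2.8.2) puts all-cause mortality first and a composite second. The composite consists of "treatment abandoned due to worsening heart failure, successful resuscitation after cardiac arrest, malignant arrhythmia, nonfatal stroke, heart failure hospitalization". Death is not a component.
- **Follow-up.** The abstract states: "The 12-week intervention phase will be followed by 40-week safety follow-up". That makes 12 + 40 = 52 weeks. Section 2.7 has eight telephone contacts after week 12, which record among other items "FRAIL scale scores, all-cause mortality, and composite endpoint events". Table 2 has composite events captured whenever they occur.
- **Analysis.** Section 2.10 names ANCOVA for peak VO2, then sorts the rest by type: "Secondary continuous outcomes: Assessed via mixed-effects models for repeated measures"; "Binary/categorical data: Analyzed using chi-squared or Fisher's exact test"; "Ordinal outcomes: Evaluated via proportional odds models". It mentions no Kaplan-Meier, log-rank, Cox or competing-risk method. It also calls the secondary endpoints exploratory.
- **Attrition.** The only figure is in the sample size section (2.2): "Considering a potential 20% attrition rate". It takes 60 per arm to 75.

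**The concern.** Death and a first composite event are dated events observed over follow-up of unequal length. A 2×2 table needs a yes or no for each patient at week 52. A patient lost earlier without an event must be counted as event-free or left out. The first choice treats unobserved time as event-free time. The second removes known event-free time while keeping patients whose event came before they would have been lost. Both shift the estimated risk, in opposite directions, and both can create a difference between arms when loss differs by arm.

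The Discussion criticises earlier trials for neglecting hard endpoints and counts assessment of longer-term prognosis among this trial's three strengths. That claim rests largely on these two outcomes.

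**Working it through.** **1. Where the 20% comes from.** Inputs from section 2.2: difference 17.6 − 16 = 1.6, SD 3.1, two-sided α 0.05, power 0.80. The normal approximation gives 2 × (3.1/1.6)² × (1.960 + 0.842)² ≈ 58.9, so 59 per arm. The two-sample t calculation gives 60 (power 0.8006; 59 gives 0.7939). Then 60/0.80 = 75 per arm, 150 in total. The plan's figure reproduces. The 20% (30 of 150) is thus an allowance for peak VO2, which Table 2 measures at baseline and week 12. No figure for loss to week 52 is given.

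**2. Effect on the estimated risk.** Assumptions: true 52-week risk 20%, constant hazard, loss spread evenly over follow-up and unrelated to events.

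- h = −ln(0.8) = 0.2231. A patient who is lost has an event before loss with probability 1 − 0.2/0.2231 = 0.1037.
- Lost counted as event-free, loss d: (1 − d) × 0.20 + d × 0.1037. For d = 0.20: 0.160 + 0.0207 = **18.1%**.
- Lost event-free dropped: 0.1807 / (1 − 0.20 × 0.8963) = 0.1807/0.8207 = **22.0%**.

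**3. Effect on the comparison when there is no treatment effect** (splits by arm assumed).

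| Loss by arm | Counted as event-free | Difference |
|---|---|---|
| 15% vs 25% | 18.6% vs 17.6% | 1.0 point |
| 10% vs 30% | 19.0% vs 17.1% | 1.9 points |

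Here the arm with more loss looks better. If those lost event-free are dropped instead, the 10% vs 30% split gives 0.1904/0.9104 = 20.9% vs 0.1711/0.7311 = 23.4%, so the arm with more loss looks worse.

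**4. Effect on the tests.** Simulation with 75 per arm, exponential event and loss times, 3,000 replicates; lost patients counted as event-free for chi-squared and Fisher. Type I error in %:

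| True risk | Equal 20% loss: chi-squared / Fisher / log-rank | Loss 10% control, 30% FZYX: chi-squared / Fisher / log-rank |
|---|---|---|
| 5% | 4.9 / 1.1 / 5.1 | 4.8 / 1.6 / 4.5 |
| 10% | 5.4 / 2.5 / 5.2 | 6.3 / 3.3 / 5.0 |
| 20% | 4.6 / 2.9 / 4.6 | 6.1 / 3.7 / 4.9 |
| 30% | 4.5 / 3.0 / 4.3 | 7.5 / 5.5 / 5.2 |

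The Monte Carlo standard error near 5% is √(0.05 × 0.95/3000) = 0.4 points.

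Power at a hazard ratio of 0.5 with equal 20% loss, for control risks of 5, 10, 20 and 30%: chi-squared 10, 19, 33, 45%; Fisher 3, 11, 25, 38%; log-rank 10, 18, 33, 47%.

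Dropping those lost event-free costs almost no power when loss is equal (47% for both this test and log-rank at 30% control risk). With 10% vs 30% loss it falls to 32%, against 45% for log-rank. That drop is mainly the bias in step 3 working against the arm with more loss.

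**The case against.** - **The article never says that mortality or the composite will be tested by chi-squared.** Correct. A reader might infer an explicit instruction, but there is none, and a condensed article may leave detail to a document not shown. What remains is that section 2.10 gives a rule for each data type, without exception for event outcomes, and only one of its classes fits them. Followed as written, that class applies.
- **The plan does not forecast 20% loss by week 52.** Also correct, though a reader might take it that way. A patient who misses the week-12 exercise test can still be reached by telephone. If status at week 52 were known for everyone, a comparison of proportions would be unbiased.
- **Risk is not always understated.** It is understated if the lost count as event-free and overstated if those lost event-free are dropped. The article does not say which would apply.
- **The size is modest.** At 20% risk and 75 per arm the standard error of a difference is √(2 × 0.2 × 0.8/75) = 6.5 points, so 1.9 points is about 0.3 standard errors. With equal loss the tests nearly agree. A stronger charge, that these outcomes could not be validly analysed, is not supported.
- **Survival methods make assumptions too.** Log-rank and Cox need non-informative censoring, which the simulation grants them. Loss driven by worsening heart failure would bias them as well.

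**Conclusion.** The point holds in a limited form. By elimination, the stated methods send two event outcomes with 52 weeks of follow-up to a test that cannot use event times or partial follow-up. On an assumed 20% risk and 20% even loss, the reported risk would be 18.1% or about 22.0%, depending on how lost patients are handled. The comparison between arms is little affected if loss is equal. It is biased if loss differs: 1.9 points at 20% risk for 10% vs 30% loss, with chi-squared type I error up to about 7.5% at 30% risk. Event risks, loss to week 52 and splits by arm are all assumptions, since the article gives none.

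These endpoints are declared exploratory, and power is at most 47% by any of the three tests in the equal-loss settings examined, even at a hazard ratio of 0.5. The primary analysis and the sample size stand. The change is worth making because it is cheap and the method suits the follow-up better, not because the present wording would make the trial fail.

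**What to change.** In section 2.10:

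1. Analyse all-cause mortality as time from randomisation to death: Kaplan-Meier curves, log-rank test and Cox hazard ratio with 95% CI, censoring at last contact.
2. Analyse the composite as time to first event. Because it omits death, plain Kaplan-Meier or Cox would treat death as ordinary censoring. Either add all-cause death to the composite, or treat death as a competing event (cumulative incidence with a cause-specific or Fine-Gray hazard ratio).
3. Keep chi-squared or Fisher for binary data at a fixed time.

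Record event dates and last-contact dates on the CRF.

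The cost is a few sentences, two date fields and a little more analysis work. R, already named in section 2.10, is sufficient. No extra visits or patients are needed. Censoring must be assumed non-informative, so loss and its reasons should be reported by arm. The endpoints remain exploratory.
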